**Fig. 3 Fig3:**
[figure not shown]
Consolidated Standards of Reporting Trials (CONSORT) flow diagram

To examine the effectiveness of the eHealth intervention on the primary outcome, the number of women who quit smoking during pregnancy measured at post-intervention and follow-up, General Estimating Equations (GEE) using a logistic model will be performed. Potential covariates that will be included in the model are maternal age, depressive symptoms, gestational age, employment status, education level, level of addiction, and partner’s smoking status. To investigate the effectiveness of the intervention on secondary outcomes (i.e., smoking behavior, perceived stress, birth outcomes, negative affectivity, self-efficacy, mother-child bonding, intrinsic motivation, parenting self-efficacy, pregnancy-related anxiety) linear mixed models will be performed for each outcome variable separately. Furthermore, we will test whether the effect of the intervention (independent variable) on smoking cessation (dependent variable) is mediated by a change in perceived stress using a GEE model. Moreover, it will be tested whether program usage and experience, self-efficacy regarding smoking cessation, feelings of mother-child bonding, intrinsic motivation for life style behavior change, and pregnancy experience moderate the effect on smoking cessation (primary outcome), smoking behaviour, and perceived stress by adding the variables to the GEE model.

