### The current study

The current study will examine the effectiveness of a personalized 8-week lasting eHealth intervention “Together with Eva”, consisting of adapted parts of existing quit-smoking and stress-management interventions and an HRV-BF prototype application by means of a randomized controlled trial. “Together with Eva” includes psycho-education on stress, smoking (cessation), and pregnancy; a personalized stop-smoking plan; stress reducing exercises, comprising of HRV-biofeedback, and problem-solving techniques. Participants in the control group will receive access to a webpage developed for this study where they can read information comparable to the psycho-education of the intervention group. This information is however summarized and not interactive. Overall, the main research question of this study is the following:
Is the app intervention “Together with Eva” an effective intervention to support pregnant women to quit smoking during pregnancy and stay abstinent after giving birth? The primary outcome measure is self-reported smoking cessation. Secondary objectives of this study are to investigate whether;the intervention is effective on secondary outcomes (i.e. smoking behavior, perceived stress, birth outcomes, negative affectivity, parenting self-efficacy, pregnancy-related anxiety, feelings of mother-child bonding, and COVID-19 related stress),the intervention effect on smoking cessation is mediated by the reduction of perceived stress, and whether;variables such as program usage and experience, self-efficacy regarding smoking cessation, intrinsic motivation for life style behavior change, and pregnancy experience moderate the treatment effect.

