## Methods and analysis

### Trial design

This study is a two-arm, parallel, single blinded randomized controlled trial (RCT) including four measurement waves: pre-intervention or baseline (t0), post-intervention (t1), two weeks following birth (t2) and three months after birth (t3). Pregnant, smoking women will be randomized to one of two groups: 1) personalized eHealth intervention (“Together with Eva”) on the smartphone followed for 8 weeks; or 2) active control condition which includes psycho-education on stress, smoking, and pregnancy through a website. The protocol is developed in accordance with the Standard Protocol Items: Recommendations for Interventional Trials guidelines (SPIRIT; Fig. 1). The trial is registered with the Netherlands Trial Register on November 112,019. The registration ID is NL8156. Ethical approval was obtained from the Medical Ethical Committee of the VU Medical Center (METc VUmc 2020/065/NL71342.029.20).

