### Participants and recruitment procedure

Participants will be recruited through midwifery practices, specialized departments of hospitals in the Netherlands and through advertisements on reliable websites focusing on pregnancy over a 1.5-year period (July 2020–February 2022). Health care professionals will be offered flyers to hand out to potential participants. Additionally, they will receive an information sheet with the inclusion criteria, short sentences for study explanation, and a list of frequently asked questions so that they can easily explain the study to potential participants. Women are eligible for participation if they are older than 18 years, are less then 28 weeks pregnant (to enable intervention completion in view of the risk for premature birth in pregnant smokers), if they smoke on a regular basis (at least smoking 1 day/week), have an intention to quit smoking during pregnancy, and if they have sufficient command of the Dutch language. Women with severe psychiatric disorders, women who abuse other drugs (e.g. alcohol, cannabis, cocaine, and GHB), and who are participating in other intensive stop-smoking interventions will be excluded from participation. The focus of our recruitment will be on women with low SES. However, women with high SES are also allowed to participate.

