### Sample size calculation

To ensure acceptable power for the main analysis of the intervention effect on smoking cessation at post-intervention, an a priori sample size calculation was performed by the program G*Power [54]. Using a power of 80% an alpha of 0.05 and an F-test, we need to include 160 participants (80 participants in each arm) in order to be able to detect a small difference (effect size of 0.20) between the intervention group and the control group on the primary outcome measure, smoking cessation at t1.

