#### Primary outcome

##### Smoking cessation

Smoking cessation and abstinence will be assessed using a self-report question ‘Do you smoke?’ (yes/no). If answered with ‘yes’, an additional question asking whether she smokes on a daily basis will indicate the frequency of the smoking behaviour.

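### The primary outcome is sized at t1 but analysed over pregnancy and postpartum waves, and the contrast that decides success is not named

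*Protocol article*

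**What the plan says.** Sample size calculation ties both the main analysis and the primary outcome to one time point: "To ensure acceptable power for the main analysis of the intervention effect on smoking cessation at post-intervention" and then "the primary outcome measure, smoking cessation at t1". The total is 160 women, 80 per arm.

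Statistical analyses defines the outcome over several waves: "the primary outcome, the number of women who quit smoking during pregnancy measured at post-intervention and follow-up". One logistic GEE is planned for it, at a significance level of 0.05. No contrast from that model is named as decisive.

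Trial design places the follow-up waves at "two weeks following birth (t2) and three months after birth (t3". Outcome measures sends the t1 questionnaire eight weeks and one day after group assignment.

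The main research question joins two aims, asking whether the app helps women "to quit smoking during pregnancy and stay abstinent after giving birth". The abstract names self-reported cessation as primary and gives no time point.

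On measurement: "Smoking cessation and abstinence will be assessed using a self-report question", a present-tense yes/no item with no stated recall period.

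**The concern.** The two sections describe different targets under one name. A woman's smoking status two weeks or three months after birth is not evidence of whether she quit during pregnancy. She may have quit and relapsed, or quit only after the birth. Averaging t1, t2 and t3 therefore mixes quitting in pregnancy with relapse after it, and the Introduction itself describes postpartum relapse as common.

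At stake is what the headline result means and who chooses it. With t1, an average and an interaction all consistent with some part of the text, the deciding test could be settled once the data are in. An unseen analysis plan could not simply fill a gap here. It would have to choose between two statements that the article already makes.

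**Working it through.** **1. Which waves can measure quitting in pregnancy.** Entry is before 28 weeks, and t1 follows assignment by eight weeks and one day. 28 + 8 = 36, so t1 falls at about 36 weeks at the latest, plus any delay between recruitment and assignment. For most women that is before birth. t2 and t3 are after birth by definition. Only t1 fits the label used in Statistical analyses.

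**2. Does the stated 160 show which contrast was meant?** The inputs are an F-test, effect size 0.20 (taken as Cohen's f, since the metric is not named), alpha 0.05 and power 80%.
- One time point: noncentrality = f² × N = 0.04 × 160 = 6.4 on 1 and 158 df, which gives power 71.0%. Power of 80% needs N = 200 (0.04 × 200 = 8.0).
- Average over m waves with between-wave correlation ρ: noncentrality = f² × N × m / (1 + (m − 1)ρ). With m = 3 and ρ = 0.7 the multiplier is 3 / 2.4 = 1.25, and 0.04 × 160 × 1.25 = 8.0, so N = 160. With m = 2 and ρ = 0.6 the multiplier is 2 / 1.6 = 1.25, again N = 160.

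So 160 does not follow from the stated inputs at t1. It does follow from a multi-wave calculation, but only with inputs the article does not give. The figure cannot settle which contrast was intended. Whether 160 is enough is a separate question.

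**3. The averaged effect is a different quantity.** Assume the same relapse in both arms, 25% by t2 and 43% by t3, with no late quitting. The 43% is the Introduction's six-month figure, used here at three months as an assumption. For a t1 risk difference D, the average is D × (1 + 0.75 + 0.57) / 3 = 0.773 D. As an illustration with assumed quit rates of 15% and 34%, D is 19.0 points and the average is 14.7.

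On the odds-ratio scale of the planned model the gap is smaller:
- t1: (0.34/0.66) / (0.15/0.85) = 2.92
- t2: (0.255/0.745) / (0.1125/0.8875) = 2.70
- t3: (0.1938/0.8062) / (0.0855/0.9145) = 2.57
- geometric mean: 2.73, against 2.92 at t1

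**4. Type I error if the deciding wave is chosen afterwards.** Assume no true effect, 80 per arm, 20% abstinent at t1 and the relapse above. Abstinence is then 0.20, 0.20 × 0.75 = 0.15 and 0.20 × 0.57 = 0.114. Because each later abstinent group is a subset of the one before, the correlation between two wave tests is √[p_later(1 − p_earlier) / (p_earlier(1 − p_later))]:
- t1 and t2: √(0.15 × 0.80 / (0.20 × 0.85)) = 0.84
- t1 and t3: √(0.114 × 0.80 / (0.20 × 0.886)) = 0.72
- t2 and t3: √(0.114 × 0.85 / (0.15 × 0.886)) = 0.85

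In 20,000 simulated null trials with a two-group comparison at each wave, at least one wave reached p < 0.05 in 9.5%, against 4.9% for t1 alone. As a check, three normal test statistics with a common correlation give 9.9% at 0.8, 10.9% at 0.7, 12.5% at 0.5 and 13.5% at 0.3. Any single contrast named in advance stays at 5%.

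**The case against.** The best reply is that the article already names t1 in Sample size calculation, and that Statistical analyses specifies one GEE, not three tests. Including later waves in a GEE does not rule out a t1 contrast from it, and a condensed article may leave the choice of contrast to a fuller plan. Much of this stands: a multi-wave GEE is no error. But the later section redefines the outcome itself over all waves, so naming t1 in the earlier one is half of the conflict and does not resolve it.

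The pregnancy label can also be read kindly, as quitting by t1 and then being followed after birth. That fits the main research question. It still leaves open which part decides success.

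A reader might infer more than the text supports:
- **That success at any wave counts, so the error rate is already inflated.** No section says so, and 9.5% is conditional on a choice made after the data. The 14.3% for independent tests (1 − 0.95³) is not credible for repeated smoking status in the same women.
- **That nothing balances reporting error because the trial is unblinded.** Trial design calls it single blinded, without saying who is blinded. Women do report their own outcome and the arms differ visibly, but the article gives no basis for sizing a bias.
- **That the undated question makes the outcome invalid.** The missing recall period is real, and eligibility admits light smokers ("if they smoke on a regular basis (at least smoking 1 day/week"). But the item can be read as asking about habitual status, and no misclassification can be quantified. It is a separate measurement point.

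**Conclusion.** The concern holds as a conflict between two stated definitions of the primary outcome, with the deciding contrast left unnamed and a label that t2 and t3 cannot meet. It should be fixed, but it does not undermine the design.

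The conflict and the timing problem rest on the text alone. The sizes rest on assumptions. The error of about 9.5% needs a deciding wave chosen after the data and the stated abstinence and relapse rates. The factor of 0.773 on the risk difference needs equal relapse in both arms and a six-month figure applied at three months. The harm is to interpretation and, potentially, to the error rate; no loss of power is claimed.

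**What to change.** In Statistical analyses, state that the primary test is the group contrast in abstinence at t1, taken from the GEE with group, wave and group-by-wave terms, two-sided at 0.05. This agrees with Sample size calculation.

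List t2, t3 and sustained abstinence (abstinent at t1, t2 and t3) as secondary, tested in a fixed order. Call t2 and t3 postpartum abstinence, and keep the reference to quitting during pregnancy for t1. Sustained abstinence needs no new data, although three point-in-time answers do not show what happened between waves.

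The cost is a few sentences, dated before outcome data are examined; the article reports that data collection is still ongoing.

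Optionally, and separately, add an item on any smoking in the past seven days at the remaining waves, keeping the present question as the primary item. The downside is that women who have already passed a wave will lack the new item, so it can only be supportive in this trial.

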Despite the growing body of evidence on the negative consequences of prenatal smoking for child development and despite extensive efforts to reduce the prevalence of prenatal smoking, a relatively large group of expecting mothers continues to smoke during pregnancy [1]. Factors associated with continued smoking during pregnancy are socioeconomic status (SES), nicotine dependence, and stress experienced during pregnancy [14, 15]. In general, women of low SES experience socioeconomic inequalities when it comes to financial resources, stability in living situation, general health, including more stress-related health problems and unhealthy lifestyle habits such as smoking [16, 17]. Stress plays an important role in initiating smoking and maintenance of smoking [18, 19]. According to the stress-coping model, smoking causes a temporarily reduction of negative affect and an increase in positive affect, which can be an explanation for the use of smoking as a coping strategy in situations of high stress [20]. Neurobiological models of addiction suggest that both stress and nicotine exposure trigger stress and reward circuits in the brain explaining why stress can increase the urge to smoke [18]. Moreover, high levels of stress hinder changing unhealthy lifestyle behaviors, such as smoking [21]. Increased activation of brain stress systems are thought to reduce an individual’s ability to cope with extra stressors and may strengthen the effects of acute nicotine exposure during abstinence, thereby contributing to the increased vulnerability to relapse caused by stress during periods of abstinence [19]. Elevated stress levels may thus explain why expecting women may fail to quit smoking, because pregnancy is a critical life event. Indeed, during pregnancy, many women experience some additional levels of psychosocial and pregnancy-related stress [22], due to physical changes related to pregnancy, concerns about childbirth and parenting, or relationship difficulties. These extra pregnancy related stressors can thus make smoking cessation even more challenging.

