During the last decades, more and more health care is being offered via the Internet, for instance by means of eHealth platforms [39, 40]. Benefits of eHealth are the high accessibility for a large group of people and the usually low cost it entails. Moreover, eHealth is unrestricted by time and place and might reach populations that otherwise do not ask for support, for instance as a result of possible stigmatization. As stigmatization is a common problem among pregnant smoking women [41], and considering the many benefits of eHealth for this group [42], an app-intervention to support pregnant women quit smoking is promising. A recent systematic review supports this, as results show that eHealth approaches were moderately effective on smoking abstinence in a general population of adult smokers [43]. They also emphasize the use of an interactive and tailored approach of smoking cessation interventions.

Considering the benefits of eHealth, we have developed an application including HRV-BF, targeting pregnant women who want to quit smoking. HRV-BF is easy to learn and maintain in daily life, and at the same time requires little efforts. Thus, HRV-BF could be highly appropriate for pregnant smoking women with low SES, who would like to quit smoking. In order to gain knowledge about the underlying mechanisms and conditional factors of treatment effectiveness, various factors that are associated with stress and smoking need to be studied. Factors that may affect the treatment effect obtained in stress reduction and smoking cessation are: pregnancy experience [21], pregnancy-related anxiety [44], self-efficacy regarding smoking cessation [45], a person’s motivation to quit smoking [46], and COVID-19 related stress [47]. Moreover, focusing on indirect treatment effects is also relevant in this transitional and developmental context. For example, factors associated with parenting, such as parenting self-efficacy [48–50] and the bond that the mother feels with her child [51, 52] may also increase when women experience less stress and quit smoking. Parenting factors such as parenting self-efficacy and a warm mother-child bond have been associated with positive effects on child development (e.g. [48, 53]).

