##### Self-efficacy regarding smoking cessation

Self-efficacy regarding smoking cessation will be assessed by six items from a questionnaire developed by [66]. Participants are asked to indicate whether they are able to refrain from smoking if they find themselves in specific situations, for instance when they feel stressed or tense and when someone offers them a cigarette. Questions can be answered by 0 (never) to 3 (always). Higher scores indicate higher self-efficacy regarding smoking cessation.

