### Statistical analyses

The study will be performed according to the Consolidated Standards of Reporting Trials (CONSORT) Statement (see Fig. 3). All analysis will be done in SPSS version 26.0 and ﻿RStudio version 1.1.456 and a significance level of 0.05 will be used. Analyses will be performed conforming to intention-to-treat analysis, so that all randomized participants will be analyzed. We will explore baseline data to examine differences between the two different conditions and between the study completers and drop-outs. We will control for relevant covariates (i.e. SES, treatment history, maternal age, gestational age at birth, level of addiction, birth complications, way of delivery) by adding them to the models. Prior to the main analyses, outliers will be checked. Demographic outcomes will be compared using chi-square tests and independent sample t-tests.

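### The covariates for the primary cessation model leave out baseline perceived stress, and cessation self-efficacy if measured at t0; adding them is an optional efficiency gain, not a correction

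*Protocol article*

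**What the plan says.** The Statistical analyses section gives two covariate lists. The general one reads: "We will control for relevant covariates (i.e. SES, treatment history, maternal age, gestational age at birth, level of addiction, birth complications, way of delivery". The one for the primary logistic GEE reads: "Potential covariates that will be included in the model are maternal age, depressive symptoms, gestational age, employment status, education level, level of addiction", with partner's smoking status as the seventh item. Perceived stress and cessation self-efficacy are in neither.

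The Introduction gives the background: "Factors associated with continued smoking during pregnancy are socioeconomic status (SES), nicotine dependence, and stress experienced during pregnancy". Further on, it lists cessation self-efficacy among factors that may influence the treatment effect. The scale itself is described under Moderators: "Participants are asked to indicate whether they are able to refrain from smoking if they find themselves in specific situations".

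Both variables are used elsewhere. Change in perceived stress is the planned mediator, and cessation self-efficacy is to be tested as a moderator of the effect on cessation.

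**The concern.** All women smoke at entry, so the binary primary outcome has no baseline variation to adjust for. Any precision gained from adjustment has to come from other pre-randomization predictors of quitting. The Introduction names three such factors. The primary model takes up SES (through education and employment) and nicotine dependence (through level of addiction), but not stress, which is the construct the intervention is built around.

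In a logistic model, leaving out a strong baseline predictor shrinks the estimated arm effect relative to the fully conditional one and lowers the power of the arm test. With 80 women per arm and one primary model, a few points of power are worth having if they cost almost nothing.

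**Working it through.** **1. The plan's own power figure.** The Sample size calculation section states: "Using a power of 80% an alpha of 0.05 and an F-test, we need to include 160 participants (80 participants in each arm". The effect size is given as 0.20, is called small, and refers to cessation at t1. A two-group F-test with f = 0.20, alpha 0.05 and 80% power needs N = 200, and power at 160 is 0.71. If 0.20 is read as d (f = 0.10), N = 788 and power at 160 is 0.24. The stated 160 does not follow from the stated inputs. It can be reached with unstated ones, for example two repeated measures correlated at 0.6. That is a separate matter. What counts here is that no quit rates, prognostic strengths or allowance for covariates are given, so any power gain from adjustment has to be shown over assumptions.

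**2. Is a t0 value available?**
- Perceived stress: yes. A change score needs a starting value, and t0 comes before randomization, so adjusting for it does not block the mediated effect.
- Cessation self-efficacy: probable. A moderator should be a baseline value, and self-efficacy is also listed as a mixed-model outcome. But the Outcome measures section says only that t0 holds the main outcomes and demographics, no wave is stated for this scale, and Fig. 1 is not shown.

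**3. First simulation.** One time point (t1), 80 per arm, 3,000 trials per setting, two-sided Wald test of arm at 5%. Two already listed covariates (odds ratio 1.5 per SD each) are in both models; the larger model adds two baseline covariates. Assumed quit rates, control against intervention: 15% v 35%, 10% v 25%, 20% v 40%. The correlation of each added covariate with a listed one is 0 or 0.5.

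| Odds ratio per SD of each added covariate | Change in power, all settings (points) | Example: 15% v 35%, correlation 0.5 |
|---|---|---|
| 1.0 (not predictive) | -0.5 to +0.1 | 86.8% to 86.7% |
| 1.25 | -0.5 to +1.1 | 86.9% to 87.0% |
| 1.5 | +1.2 to +2.6 | 87.8% to 89.0% |
| 2.0 | +3.3 to +5.8 | 88.4% to 91.7% |

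At odds ratio 2.0 the gain is 4.6 to 5.8 points with correlation 0 and 3.3 to 4.4 with correlation 0.5, so overlap with listed covariates removes part of it. The Monte Carlo standard error of one power estimate is about sqrt(0.8 x 0.2 / 3000) = 0.7 point. Shifts of half a point are therefore of the order of simulation noise.

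**4. Second simulation.** All seven listed covariates in both models, 20% quitting in control, odds ratio 2.5 for arm, depression-stress correlation 0.6, self-efficacy-addiction correlation -0.3, 3,000 trials. Log-odds per SD are given for self-efficacy and stress in turn:
- 0, 0: 71.1% to 71.4% (+0.3)
- 0.4, -0.3: 65.5% to 65.9% (+0.4)
- 0.7, -0.4: 56.9% to 61.3% (+4.4)
- 0.9, -0.5: 52.9% to 59.5% (+6.6)

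Type I error was 4.8% to 5.2% without the two terms and 5.0% to 5.9% with them. A further set, with 10% or 20% quitting in control, gave -0.6 to 0 points for useless predictors, 0 to +1.5 for weak-to-moderate ones and +3 to +4 for strong ones. Type I error there was about 5% to 7% in both models.

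**5. In terms of sample size.** The ratio is ((1.96 + z_new)/(1.96 + z_old))^2, with z the normal quantile of power. For 87.8% to 89.0%: (3.187/3.125)^2 = 1.04, about 4% more women. For the largest gain in the first simulation, 81.2% to 87.0%: (3.086/2.845)^2 = 1.18, about 18% more.

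**6. Load on the model.** At 15% v 35% there are 80 x 0.15 + 80 x 0.35 = 40 quitters at t1. Arm plus seven covariates is at least 8 slopes, or 5 quitters per slope; two more terms make it 40/10 = 4.

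**The case against.** The strongest reply is that nothing here is wrong. The primary list is headed as potential covariates, the document is a journal article, and final covariate choice is commonly settled in a fuller plan. This stands: the point is a suggestion.

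Four stronger readings are tempting, and the document does not support them.

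- A reader might infer that power is given up for nothing. The model is already heavily loaded for about 40 quitters, and stress overlaps with the listed depressive symptoms. The simulations show little harm from two more terms, but the gain is also about zero if the predictors are weak.
- A reader might infer that both variables are certain to be on file at t0. That holds for stress only. Inclusion began in July 2020, so if the self-efficacy scale is not in the t0 questionnaire, it cannot be recovered for women already enrolled.
- A reader might infer that the document names self-efficacy as a plain predictor of quitting. The Introduction names it as a possible influence on the treatment effect, in a sentence that also names motivation, pregnancy experience, pregnancy-related anxiety and COVID-19 stress. The case for preferring it to those four is its content, which asks directly about being able to refrain from smoking. That case is weaker than the one for stress.
- A reader might infer that the less adjusted odds ratio is biased. It is a different conditional odds ratio, because odds ratios are not collapsible. The planned model is already conditional on covariates, so two more change the target slightly and do not correct an error.

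**Conclusion.** The omission is real, and for perceived stress it sits poorly with the Introduction's own reasoning. For cessation self-efficacy the case depends on the scale having been given at t0. Adding both is an optional efficiency improvement. The gain is about 0 to 1.5 points of power for weak-to-moderate predictors, with 2.6 the most seen at odds ratio 1.5 per SD. For strong predictors, at odds ratios of about 2 per SD, it is about 3 to 6 points; 6.6 was reached only with self-efficacy at a log-odds of 0.9 per SD, for which the document gives no support. About half a point is lost at most if neither predicts quitting.

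These figures rest on assumed quit rates, prognostic strengths and correlations. They cover the t1 comparison without dropout, not the full repeated-measures GEE. Importance is low, and confidence in the size of the gain is moderate.

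**What to change.** In the Statistical analyses section, add the t0 PSS total to the prespecified covariates of the primary logistic GEE. Add the t0 cessation self-efficacy total as well if the t0 questionnaire includes that scale. Enter each as a continuous main effect, use t0 values only, and settle this before outcome data are seen by arm. The moderator and mediation analyses stay as separate models.

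The cost is one line of wording, two more parameters in a model with few quitters, and an odds ratio conditional on a slightly longer list. No new data are needed for stress. For self-efficacy that depends on confirming the wave against the measurement schedule in Fig. 1.

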## Abstract

**Background:**

Maternal smoking and stress during pregnancy are associated with adverse health effects for women themselves and are risk factors for adverse developmental outcomes of the unborn child. Smoking and stress seem to be intertwined in various ways. First, the majority of smoking pregnant women is of lower socio-economic status, which is associated with higher levels of perceived stress. Second, smoking women often report to smoke because they feel stressed. Third, quitting smoking often increases perceived stress levels initially. Therefore, effective interventions are needed to support women with smoking cessation by reducing stress. The aim of this study is to test the effectiveness of an eHealth intervention on stress reduction and smoking cessation.

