#### Mediator

##### Experienced stress

Experienced stress will be measured using the Dutch, short version of the Perceived Stress Scale (PSS; [62, 63]). This scale consists of 10 items about subjective experiences of unpredictability, lack of control, and burden during the last month, e.g. ‘In the last month, how often have you been angered because of things that were outside of your control?’ Participants indicate on a 4-point scale from ‘never’ to ‘always’ to what extend the items apply to them. Higher scores indicate higher perceived stress. Items and answer categories have been adapted to make it more suitable for our target group. Previous studies reported acceptable to good internal consistency of the PSS (Cronbach’s ﻿α 0.78–0.91; [64]).

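### The waves for the stress-mediation test are not fixed, and at t1 stress and smoking status can only be concurrent, so a t1 mediation estimate cannot tell cause from consequence

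*Protocol article*

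**What the plan says.** Mediation is a stated secondary objective. Under The current study, the article asks whether "the intervention effect on smoking cessation is mediated by the reduction of perceived stress". Under Statistical analyses it says that "we will test whether the effect of the intervention (independent variable) on smoking cessation (dependent variable) is mediated by a change in perceived stress"; the only model named for this is a GEE. Neither place gives the interval over which stress change is taken, the wave of the smoking status it is set against, or a lag.

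The same section defines the primary outcome as "the number of women who quit smoking during pregnancy measured at post-intervention and follow-up", so t1 is one of the outcome waves. Sample size calculation powers the trial on cessation at t1. Trial design lists "four measurement waves: pre-intervention or baseline (t0), post-intervention (t1), two weeks following birth (t2) and three months after birth (t3"), with no questionnaire between t0 and t1.

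The mediator is the Perceived Stress Scale (PSS), which asks about "subjective experiences of unpredictability, lack of control, and burden during the last month". The outcome is a yes/no question on current smoking.

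On direction, the Introduction says "Stress plays an important role in initiating smoking and maintenance of smoking", while the Abstract (Background) says "quitting smoking often increases perceived stress levels initially".

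**The concern.** Mediation needs the mediator to come before the outcome. At t1 the schedule does not allow this: the stress change from t0 ends in the same questionnaire that records smoking status. A woman who has already quit then reports stress that wholly or partly follows her quit.

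The article describes both directions of influence, and they have opposite signs. Under the hypothesis, lower stress leads to quitting. On the reverse path, quitting raises stress, at least at first. A model that reads the t1 association as stress acting on cessation mixes the two.

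Stress coping is what the Discussion says sets this app apart from other cessation programmes. A null or reversed t1 mediation result could wrongly discredit that component, and a t1 result in the expected direction would not establish it either.

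**Working it through.** The article gives no figure for mediation, so there is none to reproduce. The check has two parts.

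**1. Timing, from the article.**
- t1 falls 8 weeks and 1 day after group assignment: 8 × 7 + 1 = 57 days.
- Taking a month as about 30 days, the t1 PSS covers roughly day 27 to day 57.
- In the app arm the woman chooses a quit date in a plan made after registration (Personalized stop-smoking plan), and she is phoned about that plan directly after randomization.
- If she quits before about day 27, her t1 stress report lies entirely after the quit. If she quits later, it straddles the quit.
- For cessation at t1, no other post-baseline stress score exists. For cessation at t2 or t3, the t0-to-t1 stress change is available as an earlier measure.

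**2. Size, by simulation.** All effect sizes are assumed; the article supplies only n = 160 and alpha 0.05. Stress is in SD units. t1 stress = pre-quit stress + g × (quit by t1), where g is the change caused by quitting. Smoking status is regressed (logistic) on arm and t1 stress. The indirect effect is a × b: a is the arm difference in t1 stress, and b is the log-odds of quitting per SD of t1 stress.

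*Trial-sized runs* (1,500 trials per setting, app odds ratio 2.5, stress with no true effect on quitting; expected rejection rate for b is 5%):
- b falsely significant: 33% to 40% across runs with g = 0.3, and 71% to 80% with g = 0.5. Mean b is about +0.31 and +0.51, where the hypothesis needs a negative value. The rate depends on the control quit rate (20% in the runs that state it). The overall range found was roughly 33% to 84%, and a lower control quit rate would lower it.
- a × b falsely significant (20% control quit rate), app with no direct effect on stress: 1.7% (g = 0.3) and 6.0% (g = 0.5).
- a × b falsely significant, app lowering stress by 0.3 SD: 9.8% and 17.6%, all negative, that is, against the hypothesis.

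*Large-sample runs* (400,000 records; app lowers pre-quit stress by 0.4 SD; direct app effect 0.5 log-odds), t1 stress on t1 smoking:

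| True stress effect on quitting | g | a | b | a × b |
|---|---|---|---|---|
| −0.5 | 0 | −0.401 | −0.499 | 0.200 |
| −0.5 | +0.3 | −0.364 | −0.183 | 0.067 |
| −0.5 | +0.5 | −0.336 | 0.019 | −0.007 |
| 0 | +0.3 | −0.375 | 0.300 | −0.112 |
| 0 | −0.3 | −0.423 | −0.293 | 0.124 |

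A post-quit rise in stress shrinks a true indirect effect of 0.20 to 0.07 or to about zero. A post-quit fall would instead create false support.

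*Does a lag repair this?* Later abstinence is assumed at 70% for women who had quit by t1 and 10% for the others.
- Lag alone, true stress effect −0.5: a × b is 0.12, 0.04 and about 0 for g = 0, 0.3 and 0.5. The bias remains, because quitting by t1 still precedes the t1 stress report.
- Lag plus adjustment for t1 smoking status, no true stress effect: false positives are 4% to 5% at every g.
- Lag plus that adjustment, with real mediation running through quitting by t1: a × b is −0.002, 0.001 and −0.000. The adjusted model does not see that route.

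**The case against.** A reader might infer that the article plans to take stress change and smoking status from the same waves throughout. It does not say so. The mediation sentence names no wave, and stress change from t0 to t1 set against cessation at t2 or t3 would fit the text. An article may also leave mediator windows and lags to a fuller plan, and the figure listing measures by wave is not shown. This stands for t2 and t3. It does not remove the problem at t1, where concurrency follows from the published schedule and no later specification can supply an earlier stress score.

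A reader might also take 33% to 84% as the rate of false mediation findings. It is the rejection rate for the stress coefficient alone. Mediation also needs the app-to-stress path, and the corresponding figure is roughly 2% to 18%.

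The article's statement on quitting and stress is hedged to what often happens initially. For women who quit early, the rise may have passed before the recall month begins. The size, and even the sign, of the reverse path at t1 therefore cannot be known from the document. This stands, and it is why the simulations are illustrations only.

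Finally, adjusting for t1 smoking removes the main hypothesised route: app, lower stress, quitting by t1. This also stands. The lagged model answers a narrower question and has to be labelled that way.

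**Conclusion.** The concern holds in a limited form. The article does not fix the waves of the mediation analysis, and for cessation at t1 the schedule makes mediator and outcome concurrent. Since the article itself describes an effect of quitting on stress, a t1 estimate is not evidence for or against mediation.

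Under assumed post-quit rises of 0.3 to 0.5 SD, true mediation is largely or wholly masked. When stress has no effect on quitting, the stress coefficient is falsely significant with the wrong sign in roughly 33% to 84% of trials, and the indirect effect in roughly 2% to 18%. These figures rest on assumed effect sizes and quit rates; the structural point does not.

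Severity is minor. The documents do not support a reading in which the main result is compromised: mediation is a secondary objective, and the comparison of arms on cessation does not use the stress score.

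**What to change.** In Statistical analyses:
- Name the waves that supply the stress change and the smoking status.
- State that t1 stress with t1 smoking status is an exploratory association and not evidence for or against mediation.
- Base the mediation claim on PSS at t1, adjusted for PSS at t0, with abstinence at t2 and t3 as the outcome, adjusted for smoking status at t1 and the baseline covariates. Report the indirect effect with a bootstrap interval.
- State the limit: this model tests mediation of later abstinence or relapse only. Mediation through quitting by t1 cannot be identified from the four waves.

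The cost is analysis wording; all the data are already scheduled. The downsides are fewer women in the model, since it needs both t1 and follow-up data, and a narrower question than the stated objective.
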